Many preventive or therapeutic strategies are used for the management of pregnancy-related PPGP. Current pain relief recommendations include avoiding certain physical loads, relaxation, massage, medications, exercise, physical therapy, and pelvic or lumbar supports [16]. Among the recommendations for managing pregnancy-related PPGP, it was noted that pelvic or lumbar support is widely used to manage painful symptoms [17,18]. Pelvic or lumbar support, also known as soft orthosis, can work through a combination of mechanisms to address the SIJ instability. First, the circumferential supports are expected to apply a compressive force on the pelvis to promote anatomical alignment [19], stiffness [20], and increase the function of the SIJ [21]. Second, soft orthoses can also provide potent stimuli to improve neuromuscular control required for lumbopelvic function [22]. It has been shown that the gentle pressure soft orthoses applied to the skin receptors can positively affect proprioceptive acuity [20,23], pain intensity [17,24], joint stability [25,26], and physical function [17,27].

Emerging research has highlighted the sensorimotor effectiveness of narrow pelvic supports in pregnancy-related PPGP [27,28]. Furthermore, previous research has indicated that lumbar support effectively improved proprioceptive awareness in healthy subjects [22]. However, the effect of broader lumbar supports that allow for a wider contact area and greater skin sensory stimulation in women with pregnancy-related PPGP remains unclear. Therefore, this study first aims to investigate whether using lumbar support reduces pain in women with pregnancy-related PPGP versus controls. Secondly, it aims to examine whether broader lumbar support is more beneficial than narrower pelvic support on disability and sensorimotor outcomes (eg, joint positions reproduction) in the lumbopelvic area in women with pregnancy-related PPGP.

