### Sample Size

In total, 84 women with postpartum PPGP will be recruited. The optimal sample size was calculated on the basis of the results of a previous study [32]. The pain intensity for intervention groups was 58.2 (SD 13.93) and 64.4 (SD 13.96) at baseline, respectively [32]. We estimated a sample size of 25 in each study arm, which would yield 60% power (α=.1) and an effect size of 0.44 (Cohen *d*) in accordance with calculations performed using G*power software (Version 3.1, Universität Düsseldorf). We also considered an overall dropout rate of 10% (eg, lost to follow-up). Therefore, we aimed to recruit 84 participants (28 in each study arm).

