### Study Arms and Content

There will be 3 different study arms. As intervention groups (A and B), the first and second arms will receive pelvic or lumbar supports for 4 weeks. As the control group (C), the third arm will only receive a patient education leaflet containing advice on strengthening exercises, comfortable positions, and other practical information. The outcomes include pain, effort score during the ASLR test, maximum isometric hip flexion force, maximum isometric hip external rotation force, maximum isometric trunk rotation force, and joint position reproduction (JPR) of hip abduction. The study outcomes will be measured at 4 time points: baseline (T1), immediately after the intervention (T2), 4 weeks after the interventions began (at this time, the intervention period is completed) (T3), and 1 week after discontinuing the interventions (T4) to evaluate the possible lasting effects of wearing supports. The study process is outlined in Figure 1.

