### Outcome Measures

All tests will be carried out with a certified orthotic practitioner. Table 1 outlines the outcome measures and shows how outcome measures will be measured at different time points throughout the study.

**Table 1 table1:** The outcome measures of the study.

Measures	Baseline (T1)	Immediate effect (T2)	Fourth week (T3)	Fifth week (T4)	
Overall pain	✓	✓	✓	✓	Visual analog scale
Effort score during active straight leg raise	✓	✓	✓	✓	6-point Likert scale
Maximum isometric hip flexion force	✓	✓	✓	✓	Digital force gauge
Maximum isometric trunk rotation force	✓	✓	✓	✓	Digital force gauge
Maximum isometric hip external rotation force	✓	✓	✓	✓	Digital force gauge
Joint position reproduction of hip abduction	✓	✓	✓	✓	Kinovea software
Activity limitation	✓	✗	✓	✓	Modified Oswestry Disability Index

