### Data Analysis

All data will be saved with identification codes to maintain confidentiality. Every effort will be made to follow up on all subjects by the examiner. All enrolled participants, including those who do not complete treatment, will be included in the analysis on the basis of the intention-to-treat principle. Missing data will be replaced by the mean imputation technique, in which the mean of the observed values will be calculated and reported. Descriptive statistics will present demographic characteristics and outcome measures for each intervention group. Multivariate ANOVA will be used to test between- and within-group differences. Data will be controlled for outliers and checked for the normality and homogeneity assumptions. Post hoc (Bonferroni) tests will be conducted to report pair-wise comparisons. SPSS (version 17.0; SPSS, Inc) will be used for statistical analysis, and statistical significance will be set at a *P* value of <.05.

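### The multivariate ANOVA leaves the first aim (lumbar support versus control on pain) as one of three unranked post hoc pairs, with no deciding visit and no baseline covariate named

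*Protocol article*

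**What the plan says.** The Data Analysis section of the protocol article fixes the method: "Multivariate ANOVA will be used to test between- and within-group differences". It adds that "Post hoc (Bonferroni) tests will be conducted to report pair-wise comparisons" and that "statistical significance will be set at a *P* value of <.05". It names no covariate, no priority contrast and no decisive visit.

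The Introduction is more specific: "this study first aims to investigate whether using lumbar support reduces pain in women with pregnancy-related PPGP versus controls". The second aim there compares lumbar with pelvic support on disability and sensorimotor outcomes.

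The Primary Outcome Measures section lists two primary outcomes, pain on a visual analog scale (VAS) and the "Modified Oswestry Disability Index" (ODI). Under Study Arms and Content, "The study outcomes will be measured at 4 time points: baseline (T1" and then T2, T3 and T4. Table 1 shows pain at all four visits and ODI at T1, T3 and T4. The Participants section admits only women scoring at least 40 of 100 mm on the pain scale.

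**The concern.** An omnibus test across three arms asks whether any arm differs somewhere. The first aim asks whether one named arm beats control on one named outcome. Three arm pairs, two primary outcomes and up to three post-baseline visits leave it open which result would decide the trial.

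Three things are at stake:

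- **Power.** Baseline pain is scheduled for every participant at T1. Using it as a covariate sharpens the comparison at no extra cost.
- **False positives.** A claim could rest on whichever primary outcome and visit turns out significant.
- **Interpretation.** Within-group tests stand beside between-group tests. Women enter because their pain is high, about a month after delivery, so every arm may improve through regression to the mean and natural recovery. A significant within-group change therefore says little about the support.

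**Working it through.** **Inputs from the Sample Size section.** "The pain intensity for intervention groups was 58.2 (SD 13.93) and 64.4 (SD 13.96) at baseline"; 25 per arm, "which would yield 60% power (α=.1) and an effect size of 0.44"; 10% dropout, giving 28 per arm.

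**Reproducing the plan's figure.**
- d = (64.4 − 58.2) / √[(13.93² + 13.96²)/2] = 0.445, in line with the stated 0.44.
- A two-sample t test with 25 per arm and *one-sided* alpha .1 has power 60.3%. Two-sided .1 gives 45.7%.
- Dropout: 25/0.9 = 27.8, so 28 per arm and 84 in total.

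The trial was thus sized on a two-group comparison of pain, not on a multivariate ANOVA. The d of 0.44 comes from a baseline difference between two intervention groups, so below it serves only as an assumed effect.

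**Assumptions not in the documents.** Correlation ρ between any two visits of .3, .5 or .7; unit variance at each visit; d = 0.44 at T2, T3 and T4; 25 per arm; two-sided tests from the noncentral t with 48 df. The standardised effects for lumbar versus control are:

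- Follow-up only: 0.44.
- Baseline-adjusted (ANCOVA), one visit: 0.44/√(1 − ρ²) = 0.461, 0.508, 0.616.
- Group effect averaged over T1–T4: the effect shrinks to 0.75 × 0.44 = 0.33 because T1 carries none, and the variance is (1 + 3ρ)/4. This gives 0.479, 0.417, 0.375.

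| Analysis | alpha | ρ=.3 | ρ=.5 | ρ=.7 |
|---|---|---|---|---|
| Follow-up only, one visit | .05 | 33.2% | 33.2% | 33.2% |
| Baseline-adjusted, one visit | .05 | 35.9% | 42.1% | 56.9% |
| Group effect averaged over T1–T4 | .05 | 38.2% | 30.4% | 25.5% |
| Follow-up only, one visit | .0167 | 18.8% | 18.8% | 18.8% |
| Baseline-adjusted, one visit | .0167 | 20.9% | 25.8% | 39.0% |

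At ρ=.3 the T1–T4 average slightly exceeds single-visit ANCOVA because it pools three post-baseline visits. The like-for-like comparator, ANCOVA on the mean of T2–T4, has 62.9%, 65.6% and 78.2% at .05.

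**Multiplicity.** Suppose Bonferroni holds each outcome-visit at 5% across the three arm pairs and nothing is corrected beyond that.
- Two primary outcomes: 1 − 0.95² = 9.75% if independent.
- Five outcome-visits (pain T2, T3, T4; ODI T3, T4): 1 − 0.95⁵ = 22.6% if independent.
- Simulation with 25 per arm, between-outcome correlation 0 to .6 and between-visit correlation .5 to .7: 7.5–8.6% for two outcomes at one visit, and 15.1–18.6% for all five.

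None of these figures includes gating by the omnibus test.

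**The case against.** The strongest reply is that the article is a condensed text. Lumbar versus control is among the pairwise comparisons it promises, and covariates are commonly left to an analysis plan that is not shown here. This stands in part. A reader might infer that the first aim is never tested, and that is not so: it is tested, but without priority or a deciding visit. The point rests on the method the article does fix and its poor fit with the stated aim, not on missing detail.

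Other stronger readings also fail:

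- *Baseline is modelled as a response.* This is plausible given the within-group testing and the four time points, but the text lists no dependent variables. A post-minus-baseline contrast would recover much of the power (35.1%, 46.3% and 67.4% at .05 when T2–T4 are averaged), though still less than ANCOVA on the same mean.
- *ODI breaks a four-visit model because it is not measured at T2.* Nothing places ODI in such a model. Table 1 openly shows its three visits, and one model per outcome fits the schedule.
- *Multiplicity is uncorrected, with 23% error.* Bonferroni is stated for pairs. The 22.6% assumes independence, and gating on a joint multivariate test would hold error near 5% when no arm differs on anything. No such gate is stated, and it would not protect single contrasts once one arm truly differs.
- *Power rises from 19% to 42%.* That mixes alpha levels. At ρ=.5, adjustment adds 42.1 − 33.2 = 8.9 points at .05, or 25.8 − 18.8 = 7.0 points at .0167. The rest comes from testing one named contrast without Bonferroni.

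It is also fair that the trial is randomised with a control arm, and nowhere does the article say that within-group change will count as efficacy. The risk is that the plan leaves room for that reading.

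**Conclusion.** The concern holds in this form: the fixed main analysis is not tied to the first aim, and a better-matched analysis is available at almost no cost. At equal alpha, baseline adjustment raises single-visit power by about 3 to 24 points at .05 and 2 to 20 points at .0167, over correlations of .3 to .7. Against a group effect averaged over T1–T4, single-visit adjustment loses slightly at .3 and gains at .5 and .7. All power figures rest on the assumed d, the assumed correlation and which term is tested.

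Uncontrolled family-wise error is at most moderate: up to 9.75% for two primary outcomes and up to 22.6% for five outcome-visits under independence, and about 15–19% for the five in the correlated simulation.

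A reader should not infer that adjustment makes the trial well powered. At 42% (ρ=.5) it does not, and the sample size is a separate question.

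**What to change.** Before data are seen, reword Data Analysis as follows:

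1. Primary analysis: lumbar-minus-control difference in pain at one visit named in advance (for example T3, the end of the intervention period). Use ANCOVA or a mixed model with baseline pain as covariate, two-sided .05, and report a 95% confidence interval.
2. Analyse ODI in the same way, adjusted for its T1 value, at the visits where it is measured after baseline (T3 and T4).
3. State how the second primary outcome is handled, by fixed order or split alpha. Keep a defined place for the second aim, lumbar versus pelvic support on disability and sensorimotor outcomes.
4. Report within-group changes descriptively only.

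This needs no extra participants, visits or measurements. The downside is that other contrasts and visits become secondary, and a fixed order stops if the first test fails. With first-step power of 36% to 57% under the assumptions above, that could well happen. A split alpha avoids the stop but lowers power for each test.

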### Assignment, Randomization, and Blinding (Masking) Procedures

Once participants are confirmed to be eligible, they will be randomly assigned with equal allocation at a 1:1:1 ratio (one control participant per treatment participant) to one of 3 groups: (A) pelvic (narrower) support (n=28), (B) lumbar (broader) support (n=28), and (C) control group (patient-education leaflet) (n=28). Block randomization will be used, with a block size of 6 to achieve balance in allocating participants to study arms [35]. The assessor will perform randomization with a Random Allocation Software (version 1.0) [36]. The nature of this study will not allow for masking of the assessor after assignment to interventions. Only participants will be masked to group assignment at the point of allocation.

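### For the three arm pairs on one outcome at one visit, Bonferroni is valid but less powerful than Shaffer's step-down test; the gain from switching is about 2 to 4 points at the plan's own effect size

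*Protocol article*

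**What the plan says.** The Data Analysis section plans a multivariate ANOVA for between- and within-group differences, followed by: "Post hoc (Bonferroni) tests will be conducted to report pair-wise comparisons". Significance is set at P<.05. The section does not say which comparisons form the family that Bonferroni corrects for.

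The section on assignment and randomization fixes three arms: "they will be randomly assigned with equal allocation at a 1:1:1 ratio". That makes three arm pairs for each outcome at each time point. Table 1 lists six outcomes measured at four time points, and the disability index at three.

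The Sample Size section states: "We estimated a sample size of 25 in each study arm, which would yield 60% power (α=.1) and an effect size of 0.44". That calculation concerns a single two-group comparison and makes no allowance for a Bonferroni threshold.

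**The concern.** On the usual reading, Bonferroni tests each of the three arm pairs at .05/3 = .0167. With three arms the pair hypotheses are logically linked: if two pairs are equal, so is the third. Bonferroni ignores this link and so uses less than the 5% error allowance whenever one arm truly differs.

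What is at stake is power at a fixed number of women. A pair with P between .0167 and .05 is declared non-significant even when another pair has already passed .0167. The Introduction's second aim is lumbar versus pelvic support. If that contrast is smaller than lumbar versus control, which is an assumption, it is the pair most exposed to this loss.

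**Working it through.** **Inputs.** Three arms at 1:1:1; 25 evaluable per arm, d = 0.44, α = .1 and 60% power (Sample Size); Bonferroni and P<.05, taken as two-sided (Data Analysis). Assumed: a family of three arm pairs per outcome and time point, normal data with a common SD, and the pelvic arm's position between the other two.

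**1. The plan's own figure.** The source values are: "The pain intensity for intervention groups was 58.2 (SD 13.93) and 64.4 (SD 13.96) at baseline, respectively".
- d = (64.4 − 58.2) / √((13.93² + 13.96²)/2) = 6.2/13.945 = 0.4446.
- The noncentrality is 0.44 × √(25/2) = 1.556.
- At one-sided α = .10, power is Φ(1.556 − 1.282) = Φ(0.274) = 60.8% (60.3% with the noncentral t). The stated 60% therefore reproduces if α is one-sided.
- At two-sided .05, power is Φ(1.556 − 1.960) = Φ(−0.404), about 34% (33% with t).
- At the Bonferroni threshold of .0167 it is about 19% (simulation, pooled three-arm variance).

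**2. Why Shaffer's test holds 5%.** The rule compares the smallest of the three P values with .0167. If it passes, the other two are each compared with .05. The number of true null pairs can be three, one or none, but never two.
- All three true: an error requires the smallest P to be at or below .0167, with probability at most 3 × .0167 = .05.
- Exactly one true: an error requires that pair's P to be at or below .05, with probability at most .05.

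**3. Why it dominates.** Any pair with P ≤ .0167 makes the smallest P pass, so Shaffer rejects it too. Shaffer also rejects a pair with P between .0167 and .05 when another pair has passed. It does not raise the chance of finding at least one difference; it only adds rejections after the first.

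**4. Simulated power, 25 per arm (300,000 trials per scenario).**

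| Scenario | Pair | Bonferroni | Shaffer | Gain (points) |
|---|---|---|---|---|
| Lumbar vs control d = 0.44, pelvic = control | Lumbar vs control | 19.3% | 23.1% | 3.8 |
| Lumbar vs control d = 0.44, pelvic midway | Lumbar vs control | 19.1% | 20.9% | 1.8 |
| Lumbar vs control d = 0.44, pelvic midway | Lumbar vs pelvic | 5.1% | 8.1% | 3.0 |
| Assumed d = 0.6, pelvic = control | Lumbar vs control | 37.8% | 44.3% | 6.5 |
| Assumed d = 0.8, pelvic = control | Lumbar vs control | 64.7% | 72.7% | 8.0 |
| Assumed d = 0.8, pelvic midway | Lumbar vs pelvic (0.4 SD) | 15.7% | 26.2% | 10.5 |

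**5. Familywise error.** Bonferroni: 4.3% with all arms equal and 1.7% with one arm different. Shaffer: 4.3–4.4% with all arms equal and 5.0% with one arm very different.

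**6. The F-gated alternative.** This is a closed test: three-arm F at .05, then each pair at .05. With pelvic equal to control it gives about 25%, 47% and 75% power at d = 0.44, 0.6 and 0.8, with familywise error of 4.1% to 5.0%. It needs the univariate F for that outcome and time point. If the MANOVA across outcomes is the gate, an effect on one outcome opens it for outcomes with no effect, and the arm pairs there carry about 12% error. Nor does the shortcut carry over to four time points: with three equal and one far away, error is 12.3% in an independent-groups approximation.

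**The case against.** Bonferroni is a standard, valid procedure, and preferring Shaffer is a matter of efficiency. That stands: nothing in the plan's inference is wrong here.

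The threshold of .0167 is inferred, because the protocol does not define the family. The sentence on post hoc tests follows one covering both between- and within-group differences, so it may also govern pairs of time points (six for most outcomes, three for the disability index). That also stands. The point is therefore confined to arm pairs within one outcome and time point, and the sentence on Bonferroni should not simply be replaced, since it is the only correction stated for comparisons over time.

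A reader might infer that the plan gives up 4 to 11 points of power. The documents do not support that range for Shaffer's test. At the only effect size they give, the gain is about 2 to 4 points, and the 11-point end rests on an assumed d of 0.8. The 4-to-11 range belongs to the F-gated test for the largest pair, and there too the upper end needs effects larger than 0.44.

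A reader might also infer that Bonferroni buys nothing in return. It supplies simultaneous intervals, and its actual error is lower when one arm differs (1.7% against 5.0%). That slack is not needed for a 5% familywise level, but it is real, and the article states no correction across outcomes and visits.

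Finally, that lumbar versus pelvic is the smaller contrast is not established. The Discussion says the relative merit of the two supports cannot yet be quantified.

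**Conclusion.** The point holds as a cheap improvement. For three arm pairs on one outcome at one time point, Bonferroni is uniformly less powerful than Shaffer's test at the same 5% familywise level. The dominance is a matter of logic; its size depends on the assumed truth. At d = 0.44 and 25 per arm the gain is about 2 to 4 points. With an assumed lumbar-versus-control d of 0.8 it reaches about 8 points for the largest pair, or about 11 for lumbar versus pelvic with the pelvic arm midway. These figures assume normal data, a common SD and a family of three arm pairs.

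It would be wrong to read this as a cure for low power. At the plan's own effect size, power for lumbar versus control remains at 21–23% after the change. The larger shortfall comes from sizing one comparison at α = .1 and 60% power and then testing at .05 with Bonferroni.

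**What to change.** Keep Bonferroni for within-group comparisons between time points, and add to the Data Analysis section:

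> Pairwise arm comparisons for each outcome at each time point use Shaffer's step-down test: the smallest of the three P values is compared with .0167; if significant, the other two are each compared with .05.

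The thresholds apply to P values before any Bonferroni multiplication. If the F-gated closed test is preferred, state that the gate is the univariate three-arm F for that outcome and time point, not the MANOVA.

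The cost is one sentence and a comparison of three P values by hand, with no extra recruitment. The step-down test has no matching simultaneous intervals, so 95% confidence intervals should be labelled unadjusted, with a note that they may disagree with the test decisions.

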## Results

This study will start in summer 2022 and be complete by fall 2022.

## Discussion

### Expected Findings

It is generally accepted that rehabilitative modalities, including pelvic support, are suitable for PPGP [17]. Previous research has shown that lumbosacral orthosis effectively improved motor control and lumbopelvic function among patients with lower back pain [22]. The pathomechanics of lower back pain and PPGP are similar and include dysfunction of load transfer across the pelvis; hence, it has been hypothesized that wearing lumbar support could have beneficial effects for women with PPGP.

This study protocol will compare the impact of pelvic and lumbar supports on pain, disability, and hip repositioning in postpartum PPGP. The study results can be helpful for clinical decision-making. We anticipate that the study results will have significant implications for practitioners and specialists by increasing the scientific basis and contributing to the successful implementation of effective rehabilitation programs in clinical settings. Earlier studies have shown that both pelvic compression belts in pregnant women with PPGP [28] and lumbosacral orthosis in low back pain can significantly decrease pain [51] and improve proprioception [52], which can be explained by the biomechanical support provided [53] and proprioceptive impact of the orthosis [22]. At present, it is impossible to quantify which support is superior in reducing pain and improving proprioception and quality of life in women with PPGP. Suppose the lumbar support offers more favorable effects than the pelvic support in terms of pain reduction and improved sensorimotor outcomes. In that case, new orthotic interventions can be advised for women with postnatal PPGP.

This clinical study will evaluate repositioning in women with PPGP. For this repositioning, the JPR will be tested in a standing position. The upright position is a functionally relevant condition often occurring during daily activities. The hip abduction was selected since more precise scores for the proprioception test for the hip joint are assessed during this movement [49]. If pelvic and lumbar supports could affect the pain or load transfer at the SIJ, it could be reflected in the precision of JPR. The maximum force generation during trunk and external hip rotation is planned to quantify the possible effects of wearing the pelvic or lumbar support on the load transfer across the lumbopelvic area.

